## Abstract

**Background**: The Benefits and Risks of Iron interventionS in Children (BRISC) trial will evaluate the impact of universal supplementation with iron supplements or iron-containing multiple micronutrient powders (MNPs) compared with placebo given for 3 months on child development, growth, morbidity, laboratory indices of anaemia, iron deficiency, and inflammation at end of intervention and after a further 9 months post intervention in children aged 8 months living in rural Bangladesh. This paper describes the statistical analysis plan.

**Methods**: BRISC is a multi-site, three-arm, double-dummy blinded, parallel group, randomised control superiority trial in 3300 children. The statistical analysis plan was developed by the trial statistician in consultation with the trial steering committee and trial management committee based on the protocol, data collection forms, and study outcomes available in the blinded study database.

**Conclusion**: This detailed statistical analysis plan published prior to unblinding the allocated treatments will support the statistical analyses and reporting of the BRISC trial to be undertaken after unblinding. It allows for transparency as well as reproducibility of statistical analyses and reporting.

**Registration:** Australian New Zealand Clinical Trials Registry ACTRN12617000660381 (registered on 8 May 2017); World Health Organization Universal Trial Number U1111-1196-1125.

## Introduction

The World Health Organization (WHO) recommends daily iron supplementation to all children (universal provision) aged 6–23 months residing in settings where anaemia prevalence is 40% or above, or alternatively, home fortification with iron-containing multiple micronutrient powders where the prevalence of anaemia is 20% or above, with the goal of reducing anaemia and improving child development
^
1,
2
^. However, there is limited evidence for the effects of iron supplementation on early child development
^
3,
4
^; conversely, in high infection burden settings, iron may promote infection, including diarrhoea
^
5
^.

 The Benefits and Risks of Iron interventionS in Children (BRISC) trial is a placebo-controlled, randomised trial undertaken in rural Bangladesh designed to examine the effect of universal provision of iron syrup or iron-containing MNPs on child development, growth, morbidity from infections, and haematological and iron indices
^
6
^. The trial recruited the first participant in July 2017 and completed follow-up of the last participant in February 2020. The final results of the trial are expected to be submitted for publication by late 2020.

In this paper, the planned analyses for the BRISC trial are described. This plan supersedes the plan provided in the registry and published protocol
^
6
^. Finalisation of the statistical analysis plan prior to study unblinding has been undertaken to ensure transparency in the methods used to analyse and report the data and ultimately create the evidence for the effects of iron supplementation on early child development, growth, haemoglobin, iron status and infection.

## Methods

The trial protocol is summarised elsewhere
^
6
^.

### Aims

The primary objective of this study is to determine whether 3 months of iron supplementation or home fortification with MNPs is superior to placebo on cognitive development in 8-month old children at the end of the intervention. The secondary objectives are to evaluate the impact of iron supplementation and home fortification with MNPs, compared with placebo, on developmental indices, prevalence of anaemia and iron deficiency, growth, and infection risks at the end of the intervention and 9 months post-intervention.

### Design

BRISC is a three-arm, blinded, double-dummy, parallel group, placebo-controlled, individually-randomised, superiority trial. Starting at 8 months of age, children were randomised to either Arm 1: iron syrup (12.5 mg elemental iron) + placebo MNPs (powder sachet); Arm 2: MNPs (including 12.5 mg elemental iron) + placebo syrup; or Arm 3: placebo syrup and placebo powder/sachet (control), for 3 months (
Figure 1). Children were then followed up for an additional 9 months post-intervention. The study received ethics approval from the Ethical Review Committee of the International Centre for Diarrhoeal Disease Research, Bangladesh (icddr,b) and the Melbourne Health Human Research Ethics Committee (Melbourne, Australia). It was prospectively registered at the Australian New Zealand Clinical Trials Registry (
ACTRN1261700066038) and the World Health Organization (WHO) International Clinical Trials Registry Platform (U1111-1196-1125).

**Figure 1. f1:**
[figure not shown]
Study design.

### Setting

The trial is conducted in Rupganj, a rural subdistrict/upazila of Narayanganj district about 50 km from Dhaka, in Bangladesh. Three unions (Bhulta, Golakandail, Rupganj) within the subdistrict are included, with each union covered by a dedicated field team.

### Participants

Children eligible for enrolment were children who were 8 months of age ±14 days, were not expected to leave the study site for more than 1 week over the next 3 months or for more than one month over the next 12 months and had a legally acceptable representative capable of providing consent. Children were excluded if they had severe anaemia (haemoglobin <80 g/L), if their drinking (ground) water iron content was >1 mg/L, if their mid upper arm circumference <11.5 cm, if they had been previously diagnosed with inherited red cell disorders, or if they had a current infective illness with fever.

### Randomisation and allocation

Children were randomly allocated to one of the three arms with 1:1:1 allocation using a computer-generated schedule of randomly permuted blocks of fixed size stratified by union and sex to achieve balance between the arms within each stratum. The randomisation list was computer-generated by an independent statistician. Blinding of the team visiting the site, the caregiver(s) and study participants was achieved through the use of identical packaging of sachets and syrup. Researchers, caregivers, persons involved with data collection (i.e., field team) or analysis will be blinded to the allocation code until the database has been cleaned and is ready for analysis.

### Outcome variables

All efficacy and laboratory outcomes were measured at baseline, 3 months post-intervention and after a further 9 months follow-up. Data related to infectious morbidity and hospitalisation were collected weekly during the intervention period and monthly during the follow-up period. Serious adverse events were measured at any time. The primary time-point of interest for all outcome variables is at the end of the intervention.

The primary outcome of the study is cognitive development, as measured using the cognitive composite score of the Bayley Scales of Infant and Toddler Development, Third Edition (Bayley III)
^
7
^. Bayley-III is a validated index of child development and the preferred field assessment tool. It is a standard series of measurements primarily to assess cognitive, motor (fine and gross) and language (receptive and expressive) development of infants and toddlers aged 0–3 ½ yrs. The total number of credited items is converted into scaled scores based on child’s age, which are then converted to composite scores of each subscale.

Key secondary outcomes include motor and language composite scores assessed by Bayley III, growth (length-for-age z-score, weight-for-age z-score), and laboratory indices (haemoglobin and ferritin concentrations). Secondary outcomes include other anthropometry measures (weight-for-length z-score, stunting, wasting, underweight, head circumference) and haematological and iron diagnoses (anaemia, iron deficiency, iron deficiency anaemia). Anthropometry outcomes (z-scores) will be derived using the child’s length and weight together with age and sex of the child according to age and sex specific WHO international reference growth standards
^
8
^. Using the z-scores, stunting will be defined as length-for-age z-score <-2, underweight as weight-for-age z-score <-2, and wasting as weight-for-length z-score <-2. Using the child’s haemoglobin (g/L), ferritin (µg/L), and C-reactive protein (mg/L), anaemia will be defined as haemoglobin <110 g/L, iron deficient as ferritin <12 µg/L or ferritin <30 µg/L if C-reactive protein >5 mg/L, and iron deficient anaemia as iron deficient and anaemia.

Exploratory outcomes include child’s behaviour using items from the Wolke’s Behaviour rating scale
^
9
^, consisting of nine behaviours each scored on a nine-point scale with higher scores indicating more favourable behaviour, and the temperament questionnaire
^
10
^, consisting of 33 questions each scored on a four-point scale with higher scores indicating a better temperament which will be grouped by summing into seven temperament summary scores.

Safety outcomes include infectious morbidity (includes fever, diarrhoea, bloody stool, vomiting, cough/ difficulty breathing), (serious) adverse events, and C-reactive protein (an inflammatory biomarker) and inflammation defined as C-reactive protein >5 mg/L.

Additional data collected included household baseline characteristics (union, religion, number of household members, parity, number of children under five years of age living in the household, maternal and paternal education, maternal and paternal occupation, wealth index
^
11
^, maternal depression
^
12,
13
^, household food insecurity
^
14
^) and child baseline characteristics (sex, age, currently breastfed, home stimulation as measured using the family care indicator score
^
15
^). Daily study medication intake was collected weekly during the 3-month intervention period and included reasons for non-adherence to the allocated treatment regimen. 

### Sample size

The sample size for the trial was to recruit 3300 children (1100 per treatment arm) in order to have 80% power to detect a two-point difference in Bayley III composite cognitive score between the iron supplementation and placebo arm and the MNPs and placebo arm (two-sided 2.5% level of significance per comparison), assuming a standard deviation of 15 and a 20% loss to follow up after 3 months of intervention. No interim analyses to stop the trial early were planned, and no interim analysis was conducted.

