### Multiple testing adjustment

The two primary comparisons of interest for the primary and key secondary outcomes are iron versus placebo and MNPs versus placebo. We will use a Bonferroni adjustment combined with a gatekeeping procedure to ensure control of the Type I error rate for the primary outcome across all three pairwise comparisons. Using the Bonferroni correction, we will test each of the two primary null hypotheses of no difference between iron and placebo and MNPs and placebo for the primary outcome at the two-sided 2.5% level of significance. If at least one of the two primary null hypotheses can be rejected (multiplicity unadjusted P-Value < 0.025), a comparison of iron versus MNPs will take place at either the two-sided 2.5% (if either iron or MNPs is superior to placebo) or 5% level of significance (if both iron and MNPs are superior to placebo). Estimates and two-sided confidence intervals will be presented with the same level of significance as used for the testing of these null hypotheses, along with multiplicity unadjusted and adjusted P-Values. If neither iron nor MNPs is superior to placebo, we will report the estimate and two-sided 95% confidence interval but not the P-Value for the comparison of iron versus MNPs.

For the set of key secondary outcomes, we will use the Hochberg procedure for each of the three pairwise comparisons at the level of significance used for the primary outcome only if the corresponding null hypothesis is rejected for the primary outcome. No multiplicity adjustment is planned for secondary and exploratory outcomes, and no P-Values will be presented.

We will follow the above outlined multiple testing approach for the primary and key secondary outcomes both for the primary time-point at month 3 and the secondary time-point at month 12 separately. The primary objective of the trial will have been met if one of the two primary null hypotheses for the primary outcome at the primary time-point can be rejected at the predetermined significance level. 

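### The sample-size inputs as printed give about 71% power per comparison, not the stated 80%

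*SAP article*

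**What the plan says.** The Sample size section of the SAP article gives the planned number and its purpose: "3300 children (1100 per treatment arm) in order to have 80% power to detect a two-point difference". The contrasts are "between the iron supplementation and placebo arm and the MNPs and placebo arm". The remaining conditions are a "two-sided 2.5% level of significance per comparison), assuming a standard deviation of 15 and a 20% loss to follow up" over the 3-month intervention.

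The Multiple testing adjustment section uses the same level. Each of the two active-versus-placebo hypotheses is tested "for the primary outcome at the two-sided 2.5% level of significance", as a Bonferroni split. The 2.5% in the sample-size paragraph is therefore the level of the test that will be run, not a misprint.

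The sample-size paragraph mentions no baseline correlation, no variance reduction and no definition of power other than the per-comparison one.

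**The concern.** Every input to the calculation is printed, and together they do not lead to the printed power. The difference is too large to be rounding.

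The power statement matters most if a comparison turns out null. Readers would then judge that result against a trial said to have an 80% chance of detecting two points in that comparison. The Discussion presents the trial as settling the question and informing global policy, so the benchmark should be right. The error does not affect any estimate, test level, analysis population or decision rule.

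**Working it through.** **Inputs** (Sample size section; the level is confirmed in Multiple testing adjustment): difference d = 2; SD s = 15; two-sided level 2.5%, so z = 2.2414; power 80%, so z = 0.8416; 1100 per arm; 20% loss, leaving 1100 × 0.8 = 880 evaluable per arm.

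**Attempt to reproduce 1100.** Evaluable children per arm: n = 2 (z_level + z_power)² s² / d². Randomised per arm: n / (1 − 0.20).

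- Two-sided 2.5% with 20% loss, as stated: 2 × (2.2414 + 0.8416)² × 225 / 4 = 1069.3, so 1070 evaluable. Then 1069.3 / 0.8 = 1336.6, so 1337 per arm (3 × 1337 = 4011 in total, against 3300). This does not match.
- The same with the shortcut of multiplying by 1.2: 1070 × 1.2 = 1284 per arm. This does not match.
- Two-sided 5% with 20% loss: 2 × (1.9600 + 0.8416)² × 225 / 4 = 883.0, and 883.0 / 0.8 = 1103.7, so 1104 per arm. This matches 1100 closely.
- Two-sided 2.5% with no loss: 1070 per arm. This matches 1100 roughly.

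**Power of the stated design.** Power = Phi( d / (s √(2/n)) − z_level ).

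- 880 evaluable, 2.5%: 15 × √(2/880) = 0.715; 2 / 0.715 = 2.797; Phi(2.797 − 2.241) = 71.1%. The noncentral t gives 71.0%.
- 880 evaluable, 5%: Phi(2.797 − 1.960) = 79.9%.
- 1100 evaluable (no loss), 2.5%: 81.2%.

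**Difference detectable with 80% power** at 880 per arm and 2.5%: 0.715 × (2.2414 + 0.8416) = 2.20 points.

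**Effect of using the baseline score.** If 15 is the unadjusted SD and r is the correlation between baseline and month 3, the variance shrinks by the factor 1 − r². For 80% power at 880 per arm, r = √(1 − 880/1069.3) = 0.42, a residual SD of about 13.6. The document gives no r, so a range is shown:

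| Assumed r | Power per comparison |
|---|---|
| 0 | 71.1% |
| 0.1 | 71.5% |
| 0.3 | 75.5% |
| 0.4 | 79.1% |
| 0.5 | 83.8% |

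**Other definitions of power.** Suppose both products add 2 points. The two test statistics correlate at 0.5 through the shared placebo arm. With 880 per arm at 2.5% and no baseline gain, the chance of rejecting at least one primary null is about 85%, and of rejecting both about 57%. Neither is 80%.

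**The case against.** The strongest objection is that 71% belongs to a simpler analysis than the one planned. The efficacy analysis section specifies a constrained longitudinal model that uses the baseline score, and at a correlation a little above 0.4 that model has 80% power. This limits what can be concluded: a reader might infer that the true type II risk is 29%, and the document does not support that. The objection does not rescue the sentence, which lists its assumptions without a correlation and does not appeal to the model.

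A second objection is that the primary objective counts as met if either primary null is rejected. This also stands in part. If both products add 2 points, a primary result null on both comparisons has a probability of about 15%, not 29%. The 29% applies to one named comparison without baseline gain. But the sample-size text sets its level per comparison, and the either-product figure of 85% is not the stated 80% either.

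Third, the article condenses a protocol that is not shown, and a correlation may be stated there. That could explain the figure, but the point is not an omission: the printed inputs do not yield the printed result.

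Finally, follow-up ended in February 2020, so the number of children is fixed. That bears on the remedy, not on whether the sentence is right.

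**Conclusion.** The power statement is wrong as written. On its own inputs, and for an unadjusted two-arm comparison, power is about 71% per comparison, some 9 percentage points below the stated figure. A power of 80% holds for about 2.2 points rather than 2. These results assume normal outcomes with SD 15 in each arm and exactly 20% loss in each arm. They would improve with a baseline correlation, which the article does not state.

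Two stronger readings should be resisted. A reader might infer that the trial was sized at a 5% level and the 2.5% added later. The close match to 1104 makes that plausible, but 1100 also lies within 3% of the 1070 needed at 2.5% with no loss, so the origin is unknown. A reader might also infer that the testing procedure should be loosened to recover power. The error lies in the planning sentence and not in the Bonferroni rule, so it gives no reason to change that rule.

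**What to change.** Change the Sample size section in one of two ways:

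1. State that 880 evaluable children per arm give about 71% power per comparison for a two-point difference at two-sided 2.5% with SD 15, and 80% power for about 2.2 points.
2. If the planned longitudinal model was the basis, say so, and give the assumed correlation between baseline and month 3. It must be at least about 0.42, with 15 identified as the unadjusted SD.

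Either version may add that the chance of rejecting at least one primary null is about 85% if both products add 2 points (without baseline gain).

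The cost is a sentence or two and, under the first option, a less favourable power figure. The section on changes from the registry and protocol allows tracked changes before the code is broken to count as planned, so the correction fits there. Enrolment and the testing procedure stay as they are.

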### Statistical analysis plan

The analysis will be conducted by statisticians from the University of Melbourne. After all study data are available and clean, a blinded data review meeting to review protocol violations, overall compliance, and missing data will be held prior to database lock. The final statistical analysis plan will be signed off during this meeting. The analysis of the primary outcome will be checked by an independent statistician. Discrepancies will be discussed and resolved by consensus.

### General principles

The intention-to-treat population will be used for the analysis of all primary, key secondary, secondary, and exploratory outcomes and will include all children who were randomised. In case of missing outcome data, we will follow the missing data handling strategy outlined below. The safety population will be used for the analysis of all safety outcomes and consists of all children who received at least one study treatment (including control). Children who have withdrawn informed consent for use of all their data will be excluded from all analyses. Children will be reported and analysed according to their randomised treatment allocation. Time-windows will be applied to all visit-wise data collected at baseline, month 3, and month 12, with assessments outside the predefined visit windows excluded from the analyses. Outcomes will be summarised using frequencies and percentages (based on the non-missing sample size) for categorical variables, mean and standard deviation for continuous variables, or median and quartiles (25th and 75th percentile) for non-symmetrical continuous variables. All analyses models will be adjusted for the stratification variables used during the randomisation (union and sex). All confidence intervals and P-Values will be two-sided.

### Trial profile

The flow of children through the trial will be presented in a Consolidated Standards of Reporting Trials (CONSORT) diagram, reasons for exclusion will be reported (
Figure 2).

**Figure 2. f2:**
[figure not shown]
The CONSORT flow chart. MNPs denotes multiple micronutrient powders.

### Baseline characteristics

Demographic and baseline variables of household and child characteristics will be summarised descriptively and presented by treatment group (
Table 1). No formal comparisons between groups will be made.

**Table 1. T1:** Child and household characteristics at enrolment, according to treatment group (intention-to-treat population).

	Iron (N=XXXX)	MNPs (N=XXXX)	Placebo (N=XXXX)
**Household characteristic**			
Union - no. (%)			
Bhulta	XXX (XX.X)	XXX (XX.X)	XXX (XX.X)
Golakandail	XXX (XX.X)	XXX (XX.X)	XXX (XX.X)
Rupganj	XXX (XX.X)	XXX (XX.X)	XXX (XX.X)
Religion - no. (%)			
Islam	XXX (XX.X)	XXX (XX.X)	XXX (XX.X)
Other (Hindu, Buddhism, Christian)	XXX (XX.X)	XXX (XX.X)	XXX (XX.X)
Number of household members †	X (X-X)	X (X-X)	X (X-X)
Parity †	X (X-X)	X (X-X)	X (X-X)
Number of children under five years of age living in the household †	X (X-X)	X (X-X)	X (X-X)
Maternal education (years) †	X (X-X)	X (X-X)	X (X-X)
Paternal education (years) †	X (X-X)	X (X-X)	X (X-X)
Maternal occupation - no. (%)			
Unemployed	XXX (XX.X)	XXX (XX.X)	XXX (XX.X)
Skilled job	XXX (XX.X)	XXX (XX.X)	XXX (XX.X)
Unskilled job	XXX (XX.X)	XXX (XX.X)	XXX (XX.X)
Other	XXX (XX.X)	XXX (XX.X)	XXX (XX.X)
Paternal occupation - no. (%)			
Unemployed	XXX (XX.X)	XXX (XX.X)	XXX (XX.X)
Skilled job	XXX (XX.X)	XXX (XX.X)	XXX (XX.X)
Unskilled job	XXX (XX.X)	XXX (XX.X)	XXX (XX.X)
Other	XXX (XX.X)	XXX (XX.X)	XXX (XX.X)
Wealth index - no. (%)			
Quintile 1 (relative poorest)	XXX (XX.X)	XXX (XX.X)	XXX (XX.X)
Quintile 2	XXX (XX.X)	XXX (XX.X)	XXX (XX.X)
Quintile 3 (relative middle)	XXX (XX.X)	XXX (XX.X)	XXX (XX.X)
Quintile 4	XXX (XX.X)	XXX (XX.X)	XXX (XX.X)
Quintile 5 (relative wealthiest)	XXX (XX.X)	XXX (XX.X)	XXX (XX.X)
Maternal depression score †	X (X-X)	X (X-X)	X (X-X)
Household food insecurity score †	X (X-X)	X (X-X)	X (X-X)
**Child characteristic**			
** General**			
Female sex - no. (%)	XXXX (XX.X)	XXXX (XX.X)	XXXX (XX.X)
Age (months) *	X.X (X.X)	X.X (X.X)	X.X (X.X)
Currently breastfed - no. (%)	XXX (XX.X)	XXX (XX.X)	XXX (XX.X)
Family Care Indicator total score *	X.X (X.X)	X.X (X.X)	X.X (X.X)
** Laboratory indices**			
Haemoglobin concentration (g/L) *	XX.X (X.X)	XX.X (X.X)	XX.X (X.X)
Anaemia - no. (%)	XXX (XX.X)	XXX (XX.X)	XXX (XX.X)
Ferritin (ug/L) †	XX.X (XX.X-XX.X)	XX.X (XX.X-XX.X)	XX.X (XX.X-XX.X)
Iron deficient - no. (%)	XXX (XX.X)	XXX (XX.X)	XXX (XX.X)
Iron deficient anaemia - no. (%)	XXX (XX.X)	XXX (XX.X)	XXX (XX.X)
C-reactive protein (mg/L) †	XX.X (XX.X-XX.X)	XX.X (XX.X-XX.X)	XX.X (XX.X-XX.X)
Inflammation - no. (%)	XXX (XX.X)	XXX (XX.X)	XXX (XX.X)
